## Population

Men and women, with similar demographic characteristics, who have suffered an acute coronary event (unstable angina, NSTEACS or STEACS), regardless of whether they have undergone revascularisation or not, and who do not have angina or residual electrical ischaemia on a stress test 7-10 days after hospital discharge, will be included. The 60 patients are divided into two groups:

1. Control group A comprising 30 patients from Hospital Universitario Politécnico La Fe and Hospital Arnau de Vilanova in Valencia, who will undergo conventional in-patient rehabilitation for 8 weeks at Hospital La Fe.
2. Intervention group B comprising 30 patients from the Hospital Arnau de Vilanova and Hospital Universitario y Politécnico La Fe de Valencia, who will carry out a telerehabilitation program with the support of the Integral Telerehabilitation System (ITS) at the Hospital Arnau de Vilanova.

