## Population under study and total number of subjects

The study population consists of men and women with a maximum age of 72 years diagnosed with acute coronary syndrome who will be enrolled in a cardiac rehabilitation program. Sixty patients will be included in two groups of 30 subjects assigned to each rehabilitation program.

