# Sources of Information and Scope

The information sources for the present study are:

● Participating investigators.

● Data from the patient's medical history.

● Quality of life questionnaires (EQ-5D), Adherence to Mediterranean diet, physical activity (IPAQ), anxiety-depression questionnaire (HAD).

● Analytical data.

● Pulse wave velocity.

● Data derived from stress tests (treadmill).

● Socio-occupational data

The two rehabilitation protocols that are compared are those that have been adopted in each hospital centre. At La Fe hospital it has been in operation for years and at the Arnau de Vilanova hospital it is to be initiated with the present study. There are no additional tests except for the completion of the questionnaires mentioned above.

All necessary data will be collected in a data collection logbook (DCL).

Patients will be recruited from the Cardiology ward, in both hospitals.

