## Description of the randomisation process

After agreeing to participate in the study, subjects will be assigned to follow the conventional rehabilitation or telerehabilitation program, according to a block randomisation, estimated using a conventional statistical program.

Subject eligibility will be established prior to allocation to rehabilitation type and inclusion will be sequential. If a subject withdraws from the study his/her randomisation number will not be re-used and re-entry into the study will not be allowed.

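### Programme and delivery hospital are completely aliased, so the claim should be limited to the two services as delivered; separately, recruiting hospital is left to chance balance, a modest and avoidable loss of precision

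*Protocol*

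**What the plan says.** **Where each programme is delivered.** The Population section describes both groups as drawn from both hospitals. Control patients are those "who will undergo conventional in-patient rehabilitation for 8 weeks at Hospital La Fe"; intervention patients are those "who will carry out a telerehabilitation program with the support of the Integral Telerehabilitation System (ITS) at the Hospital Arnau de Vilanova". Sources of Information and Scope states "The two rehabilitation protocols that are compared are those that have been adopted in each hospital centre", and adds on their maturity: "At La Fe hospital it has been in operation for years and at the Arnau de Vilanova hospital it is to be initiated" with this study.

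**Who recruits.** The same section says "Patients will be recruited from the Cardiology ward, in both hospitals". The Summary gives the size: "Sixty patients will be included in two groups of 30 subjects assigned to each rehabilitation program".

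**How patients are allocated.** Description of the randomisation process says only that assignment is "according to a block randomisation, estimated using a conventional statistical program". Type of Study adds that a unit external to the researchers performs it, and that neither patients nor professionals can be blinded. No stratification factor is named in either place.

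**How the analysis treats hospital.** Methodology of statistical analysis compares the arms by t-test or Mann-Whitney test. It then plans multiple linear regression on patient characteristics, with removal at p = 0.10 and re-entry at p = 0.05. Hospital is not named. Recruiting hospital is not among the items under Data collection or Variables, and Annex 1 has no field for it.

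**What is to be claimed.** The General Objective in the Summary is to demonstrate that a telerehabilitation programme improves physical activity compliance relative to a conventional one, with no reference to where each is delivered.

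**The concern.** Two hospitals enter this trial in two roles, and each role raises its own question.

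As **place of delivery**, hospital coincides with arm. One service has run for years; the other starts with the trial. A difference in METs-minutes/week could come from the telemonitoring, or from the unit, its staff and its experience. The objective credits the programme alone.

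As **place of recruitment**, hospital is a baseline characteristic that may plausibly relate to the outcome. Control patients recruited at Arnau must attend La Fe 16 times in 8 weeks; telerehabilitation patients recruited at La Fe attend hospital 4 times in two weeks and then exercise on their own. The outcome is self-reported on the IPAQ in an open trial. In 60 patients the hospital mix can drift apart between arms. Unstratified blocks do not prevent this, and the stepwise rule could drop hospital even if it were offered as a covariate.

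**Working it through.** **Inputs from the protocol:** 30 patients per arm, 60 in total; 27 per arm assumed evaluable; target difference 5000 - 4000 = 1000 METs-minutes/week; two-sided alpha 0.05; stated power 95%. **Not in the protocol, hence assumed below:** the SD, the recruitment split, the block size, and any difference between hospitals.

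**The stated power.** It cannot be reproduced because no SD is given. Solving backwards, 95% power with 27 per arm and a difference of 1000 needs an SD of about 1000 (t-test) or 1019 (normal approximation). I use an SD near 1000, with 2000 as a less favourable alternative.

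**Part 1: delivery hospital.** Write the mean outcome as b0 + b1 × arm + b2 × delivery hospital, with arm = 1 for telerehabilitation and hospital = 1 for Arnau. For all 60 patients the two columns are identical. The design matrix has rank 2 for 3 parameters, and only b1 + b2 can be estimated. Stratifying, or adding recruiting hospital as a covariate, leaves these columns unchanged.

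To illustrate what this could mean, suppose the programmes are equivalent (b1 = 0) and delivery hospital has an assumed effect h. The t-test noncentrality is h / (SD × √(2/27)). The chance of a significant result, against a nominal 5%, is:

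| Assumed h (METs-min/week) | SD 1009 | SD 2000 |
|---|---|---|
| 250 | 14.5% | 7% |
| 500 | 43% | 15% |

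**Part 2: recruiting hospital.** Let D be the difference between arms in the number of patients from one hospital, and p that hospital's share of recruitment. Without stratification each arm's count is binomial(30, p), so Var(D) = 2 × 30 × p(1 - p) = 60p(1 - p).

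- p = 0.5: variance 15, SD 3.87. P(|D| ≥ 6) ≈ 2 × [1 - Φ(5.5/3.87)] ≈ 0.156; exact binomial 0.155.
- p = 0.3: variance 12.6, SD 3.55. P(|D| ≥ 6) ≈ 2 × [1 - Φ(5.5/3.55)] ≈ 0.12; exact binomial 0.120.

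Simulation with permuted blocks of 4 or 6 gives the same values, and 0.076 at 20:80. Blocking balances the arm totals, not the hospitals within them. If the hospital totals are instead held fixed, the hypergeometric probabilities are 0.20 (30 of 60 from one hospital), 0.17 (20 of 60) and 0.10 (12 of 60).

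A difference of 6 patients, such as 18 against 12, is 6/30 = 20 percentage points. The shift in the unadjusted estimate is 0.20 × the hospital gap in mean activity:

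- assumed gap 500: 0.20 × 500 = 100 METs-minutes/week;
- assumed gap 1000: 0.20 × 1000 = 200 METs-minutes/week.

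That is 10-20% of the target difference. At SD 1000 the standard error is 1000 × √(2/27) = 272, so the shift is 0.37-0.73 standard errors. At SD 2000 the standard error is 544 and the shift 0.18-0.37.

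With allocation stratified by recruiting hospital, D is at most half of one unfinished block: 2 patients for blocks of 4, 3 for blocks of 6.

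**The case against.** The strongest reply on **delivery** is that the protocol is open about it. It says the protocols compared are the ones each hospital has adopted, and setting and travel are part of what distinguishes telerehabilitation from hospital-based care. With only 4 hospital attendances, the site component of telerehabilitation is also small. This stands as a defence of the comparison as a pragmatic contrast of two services. It does not support an objective that credits the programme alone, because differences in staff and service maturity are not part of the strategy under test.

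On **recruitment**, the reply is that chance imbalance is ordinary sampling error, already covered by the standard error and the 5% alpha, and that its size rests on an assumed hospital gap whose upper value equals the whole target effect. That also stands, and it limits the point to precision.

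Four stronger readings are tempting, and the protocol does not support them.

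- *That patients are allocated by hospital.* The Population section draws both groups from both hospitals, so recruiting hospital is balanced in expectation and the comparison of the two services is properly randomised.
- *That missing stratification causes the aliasing.* The aliasing comes from single-site delivery alone.
- *That the protocol rules out stratification.* It is silent. An external unit allocates and may intend to stratify. The randomisation section, where the factor would be stated, nevertheless stops at blocks.
- *That hospital is excluded from every analysis.* The regression covariates are not listed, and a statistical analysis plan could name hospital. What the protocol does fix is a selection rule under which hospital could be removed.

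**Conclusion.** Both points hold, with different weight.

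1. **Delivery.** Aliasing of programme with delivery hospital is complete and follows from the text without assumptions. The trial can validly compare telerehabilitation as delivered at Arnau with conventional rehabilitation as delivered at La Fe. It cannot attribute a difference to the type of programme alone. How far this would mislead depends on a delivery-hospital effect that this design cannot estimate.

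2. **Recruitment.** Chance imbalance in recruiting hospital is a modest loss of precision, not bias. A difference of 6 or more patients has a probability of about 12-16% for an assumed split of 30:70 to 50:50 (10-20% if hospital totals are held fixed between 12 and 30 of 60). The shift of 100-200 METs-minutes/week arises only with such an imbalance and an assumed hospital gap of 500-1000. Stratification is worth having because it is cheap, not because the trial is invalid without it.

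**What to change.** 1. **Reconcile the number of centres first**, since it sets the number of strata. The Summary lists one hospital, Sources of Information and Scope, Type of Study and Population name two, and the section on accordance with regulations refers to three.
2. **Reword the General Objective and the planned conclusion** as telerehabilitation as delivered at Arnau against conventional rehabilitation as delivered at La Fe, and state the programme-plus-site limitation.
3. **Record recruiting hospital** in the data collection notebook.
4. **Stratify the allocation by recruiting hospital**, with the external unit holding one list per hospital and using concealed, varying block sizes. If this is already intended, say so in the randomisation section.
5. **Keep recruiting hospital as a fixed term**, exempt from stepwise removal, in the regression for 10-month METs-minutes/week. The t-test and Mann-Whitney test do not use the stratum, so this regression is where the gain in precision appears.

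Effects shown by recruiting hospital are optional and would be very imprecise: about 15 patients per arm and hospital if recruitment is equal.

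**Cost.** One degree of freedom, one data field, two lists in place of one, and arm totals that may end slightly away from 30 each. Shorter lists in an open trial also make the next allocation somewhat easier to guess; concealed, varying block sizes limit this. Delivering both programmes at both hospitals would remove the aliasing, but it is a different and more expensive trial.

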## Definition of the study population: selection criteria

1. Inclusion Criteria

- Patients after uncomplicated acute coronary syndrome of both sexes.
- Completion of a maximal or symptom-limited exercise test without angina or electrical ischaemia.
- Age equal to or less than 72 years.

1. Exclusion Criteria

- Refusal of informed consent
- At the investigator's judgement, primarily due to advanced biological age.
- Severe renal insufficiency (GFR < 30ml/min/1.73 m2).
- EF less than 50%.
- Hepatic insufficiency (GOT >2 times normal value).
- Uncontrolled blood pressure (>140/90 mmHg).
- Uncontrolled heart failure.
- Dissecting aortic aneurysm.
- ventricular tachycardia or other dangerous ventricular arrhythmias that are not controlled (multifocal ventricular activity).
- Aortic or mitral valve disease.
- Recent systemic or pulmonary embolism.
- Active or recent thrombophlebitis.
- Acute infectious diseases.
- Uncontrolled supraventricular arrhythmias or tachycardias.
- Repeated or frequent ventricular ectopic activity.
- Moderate pulmonary hypertension.
- Ventricular aneurysm.
- Uncontrolled diabetes, thyrotoxicosis, myxoedema,
- Hepatic or renal failure and other metabolic insufficiencies.
- Conduction disorders such as: Complete AV block. Left bundle branch block. Wolf-Parkinson-White syndrome.
- Fixed rate pacing.
- Severe anaemia.
- Psychoneurotic disorders.
- Neuromuscular, musculoskeletal and arthritic disorders that may limit activity.

1. Withdrawal Criteria

- Withdrawal of consent to continue the study.
- At the investigator's discretion if appropriate for the patient.
- Need to modify lipid-lowering treatment.
- Unwillingness to continue the study or loss due to dropout.
- Clinical events.
- Other reasons at the discretion of the investigator.

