## Data collection

The following data shall be collected on all patients at baseline, at 4 months and at 10 months.

1. Demographic data: initials of name, age, sex, identification number).

2. Clinical data: STEMI, NSTEMI, unstable angina, stable angina, number of vessels, number of stents, complete revascularisation, active smoking, ex-smoker, hypertension, dyslipidaemia, diabetes mellitus, left ventricular ejection fraction, beta-blockers, ACEI/ARBs, statins, dual antiplatelet therapy.

3. Socio-occupational data: active worker, return to work after discharge.

1. Physical examination: systolic blood pressure, diastolic blood pressure, heart rate, body mass index (BMI), waist circumference, hip circumference.
2. Analytical data: glucose, creatinine, total cholesterol, LDL cholesterol, HDL cholesterol, triglycerides, CRPus, HbA1c.
3. Pulse wave velocity.
4. Surveys: EQ-5D, IPAQ, HAD, Adherence to Mediterranean diet, Fagerström test (if active smoking).
5. Clinical events: emergency department, readmission, revascularisation.

The following data will only be collected at baseline and at 10 months.

1. Exercise test: VO2max, exercise time, maximum heart rate, maximum blood pressure, recovery time, ST decline, angor.

The following data will only be collected from patients in the intervention group:

1. Every 15 days: weight, smoking, waist circumference, systolic pressure, diastolic pressure, heart rate, visual anxiety-depression thermometer, fruit consumption, vegetables, wine/beer consumption.

2. At 4 and 10 months: survey of satisfaction with the application.

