## Outline of proceedings

|  | **Start** | **4 months** | **10 months** |
| --- | --- | --- | --- |
| **INFORMED CONSENT** | X |  |  |
| **FILIATION DATA** | X | X | **X** |
| **CLINICAL DATA** | X |  |  |
| **SOCIO-OCCUPATIONAL DATA** | X | X | X |
| **PHYSICAL EXPLORATION** | X |  |  |
| **PWV** | X |  | X |
| **BLOOD TEST** | X | X | X |
| **STRESS TEST** | X |  | X |
| **PHYSICAL WORKING CAPACITY** | X |  | X |
| **SURVEY** | X |  | X |
| **CLINICAL EVENTS** | X | X | X |
| **COST-EFFECTIVENESS ANALYSIS** |  |  | X |

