## Economic evaluation: cost-effectiveness analysis

The study includes a cost-effectiveness analysis to assess the costs and impact on health-related quality of life of the telerehabilitation intervention compared to in-hospital rehabilitation and the control group. The cost analysis will be carried out from the funder's perspective, including direct health care costs (pathology-related emergency visits, hospitalisations for the same cause, diagnostic and therapeutic tests such as revascularisations...) during follow-up. It will also include the costs derived from the intervention, which in the case of conventional rehabilitation, the programd schedule includes 16 rehabilitation visits, 8 rehabilitation sessions (with a physiotherapist, a nurse and a nursing assistant per session) and 8 educational talks. In the telerehabilitation group, the schedule includes 4 rehabilitation visits, 3 sessions (with a physiotherapist and a nurse) and 4 educational sessions. Unscheduled visits and sessions during the follow-up will also be included. The unit costs will be obtained from the Generalitat Valenciana catalogue.

Additionally, an analysis will be performed from a social perspective, including also indirect health care costs due to lost productivity of the patient (number of sick leaves and time to return to work after the event). Indirect costs will be reported by the patient in the follow-up data collection logbook. Effectiveness will be assessed by the physical activity performed by the patient, reported by the patient at the end of the follow-up, measured in METs-minutes/week.

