## Criteria for definitive withdrawal from study

A patient may withdraw her consent, if she so chooses, at any time and for any reason, or it may be withdrawn by decision of the Investigator. As far as possible, care should be taken to document the reason for withdrawal and record it in the DCL as:

- At the patient's own request.

- Physician's decision.

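### Clinical events are a ground for withdrawal from the study, yet the protocol needs later events, costs and month-10 outcomes from those same patients

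*Protocol*

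**What the plan says.** Section 6.3, under the heading "Withdrawal Criteria", gives "Clinical events" as a bullet of its own, with no type, severity or threshold. Investigator discretion appears separately in the same list, twice.

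Other sections rely on data after such an event:

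- Data collection (6.5) introduces its list with "The following data shall be collected on all patients at baseline, at 4 months and at 10 months" and includes in it "Clinical events: emergency department, readmission, revascularisation". The schedule in 6.6 marks the row "CLINICAL EVENTS" at start, 4 months and 10 months. The notebook in Annex 1 has matching fields at both follow-up visits.
- The economic evaluation (9.4) counts as direct costs "pathology-related emergency visits, hospitalisations for the same cause, diagnostic and therapeutic tests such as revascularisations", over the follow-up period.
- Methods (6.4) sets 10 months of follow-up in both groups and a final stress test, laboratory analysis and surveys for every included patient.
- The statistical methodology (9.3) specifies intention-to-treat.

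Section 12.2 says what happens on leaving the study. There is one evaluation using the end-of-study procedures, an effort to trace patients who do not return (as a minimum, to learn whether they are alive), and no readmission to the study. Continuation to the end is written only for patients removed because of LDL at 4 months. Section 12.1 asks for the reason for withdrawal ("As far as possible, care should be taken to document the reason for withdrawal and record it in the DCL as") and offers two entries: the patient's request or the physician's decision.

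**The concern.** The protocol removes patients from the study because of the same kind of occurrence that it asks sites to follow and cost. Loss of this kind is not random: whether a patient's month-10 data exist depends on how that patient fared.

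Two design features make unequal loss between the arms plausible. Patients and treating professionals are not blinded (6.1), so an undefined criterion can be applied differently by arm. Only the telerehabilitation arm submits data every 15 days (6.5), through a system that raises alerts (6.4), so its events may be noticed sooner or more often.

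At stake are the comparison of month-10 physical activity (the primary variable), the month-10 stress test, the completeness of event data and the cost comparison. With 30 patients per arm, a few such withdrawals can matter.

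**Working it through.** **1. Path of a patient withdrawn after an event.** Suppose an event at month 3 leads to withdrawal.

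| Item | Required of an included patient | Obtained after withdrawal |
| --- | --- | --- |
| Triggering event | Recorded (6.5, 6.6) | Can be recorded at exit (12.2) |
| Events in the remaining 10 − 3 = 7 months | Recorded at months 4 and 10 | No scheduled collection |
| Costs in those 7 months | Included (9.4) | No scheduled collection |
| IPAQ and stress test | At month 10 (6.4) | At about month 3 |

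The IPAQ asks about the last 7 days (7.2). A value taken soon after an event therefore describes the period around the event and does not stand in for month 10. Tracing under 12.2 applies to patients who do not return and has vital status as its minimum. No section keeps a patient withdrawn for an event under scheduled follow-up.

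**2. The plan's power figure, as background.** Section 9.1 states 95% power with 27 per arm, a difference of 1000 METs-min/week and two-sided alpha 0.05, but gives no standard deviation, so the figure cannot be reproduced from the stated inputs. Solving backwards with the normal formula:

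SD = 1000 × √(27/2) / (1.960 + 1.645) = about 1019

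The t-test calculation gives about 1000. Taking SD = 1000 as an assumption, suppose event withdrawals come on top of the planned 12% loss (30 × 0.88 = 26.4 per arm):

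| Assumed event withdrawal per arm | Remaining per arm | t-test power |
| --- | --- | --- |
| 5% | 26.4 − 1.5 = 24.9 | about 93% (n = 25) |
| 10% | 26.4 − 3.0 = 23.4 | about 91% (n = 23) |
| 20% | 26.4 − 6.0 = 20.4 | about 87% (n = 20) |

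If the 12% already includes these withdrawals, power does not change. Lost power is therefore not the main issue.

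**3. Bias, as an illustration.** Let a proportion p of an arm be withdrawn after events, let those patients be D METs-min/week below the rest of their arm at month 10, and let their exit values not be used. The observed arm mean is then too high by p × D, and the between-arm difference is biased by D × (p1 − p2), in favour of the arm with more withdrawals.

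With D = 1500, p1 = 5/30 and p2 = 2/30, all assumed:

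- arm with 5 withdrawn: 1500 × 5/30 = 250
- arm with 2 withdrawn: 1500 × 2/30 = 100
- bias: 250 − 100 = 150, and 150/1000 = 15% of the planned difference

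Range over other assumed inputs, D × (imbalance in patients)/30:

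| D | Equal numbers | 1 more patient | 3 more patients |
| --- | --- | --- | --- |
| 500 | 0 | 17 | 50 |
| 1000 | 0 | 33 | 100 |
| 1500 | 0 | 50 | 150 |

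For scale, with the assumed SD of 1000 the standard error at 27 per arm is 1000 × √(2/27) = 272, so 150 is about 0.55 of a standard error.

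**The case against.** The strongest reply is that the bullet is an ambiguous, discretionary reason and not an automatic trigger. Section 12 routes withdrawal through the investigator's or the patient's decision, and it describes the patient's decision as one to leave the rehabilitation programme. Leavers are evaluated, serious events have their own reporting route (8.1), and participants are described as low risk (13.2). Part of this stands, and several stronger readings that a reader might infer are not supported:

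- **Only one event per patient can be recorded.** The notebook has separate yes/no fields for emergency consultation, hospitalisation and revascularisation at each visit, and events before exit can be recorded at exit. Because the fields are yes/no, they hold no event counts for any patient, withdrawn or not.
- **The final IPAQ and stress test are simply lost.** The end-of-study procedures include both, so they are brought forward. What is missing is the month-10 value.
- **Section 12.1 contradicts 6.3.** The physician's decision entry can absorb an event-driven withdrawal. The weakness is that such withdrawals cannot be told apart from others.
- **The first emergency visit forces withdrawal.** Section 6.3 sets no threshold, so this imports the 6.5 list into 6.3.
- **Clinical events are a trial endpoint.** They are not among the objectives (section 4) or the variables (7.3). They are a scheduled data item and a cost input.

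Section 12.2 also leaves to the statistical analysis plan how certain patients are considered. That concerns analysis; no analysis plan can recover data that were never collected. Nor does the programme-only reading settle the matter, because the opening of section 12 itself treats leaving the programme as withdrawal from the study.

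**Conclusion.** The point holds as a conflict between stated rules. Section 6.3 allows an undefined clinical event to end study participation, while 6.4, 6.5, 6.6, 9.3 and 9.4 need data from the same patient to month 10. For a patient withdrawn on this ground, later events, later costs and the true month-10 IPAQ and stress test are not obtained, and the reason they are missing is related to clinical course.

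The size is unknown, because the protocol gives neither an event rate nor any deficit in activity after an event. The 150 METs-min/week (15% of the planned difference) rests wholly on the assumed 5 versus 2 withdrawals, the assumed 1500 deficit and exit values not being used. Under a common deficit and equal numbers withdrawn it would be zero. If exit values were used, neither the sign nor the size can be worked out from the documents. A reader might infer that a harm would be hidden or a benefit manufactured; the protocol gives no figures to show either, only a route by which bias could enter.

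**What to change.** Reconcile sections 6.3, 6.4, 6.5, 9.3, 9.4, 12, 12.1 and 12.2 by separating two things that are now merged: discontinuing the exercise programme and ending study data collection.

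- Leave programme discontinuation as the clinical decision it is now, without change.
- State that a clinical event does not by itself end data collection. With the patient's consent, the scheduled month-4 and month-10 visits, event recording and cost collection continue, and the patient is analysed in the assigned arm.
- In 12.1, add event-related programme discontinuation as a reason of its own, so that these cases can be identified and compared by arm.

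The cost is a short amendment and a few additional assessments at visits already scheduled for patients already enrolled. Some patients may decline after an event; that would be recorded as withdrawal of consent and not as loss imposed by the protocol. The change has to be made while follow-up is running, because data not collected then cannot be recovered in the analysis.
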